**Methods and design:**

Eighty-seven stroke survivors with low motivation and upper extremity dysfunction will be randomized to receive either conventional treatment, RS treatment, or RStDCS treatment. The RStDCS group will receive reward strategies combined with anodal tDCS stimulation of the left dlPFC. The RS group will receive reward strategies combined with sham stimulation. The conventional group will receive conventional treatment combined with sham stimulation. tDCS stimulation is performed over 3 weeks of hospitalization, 20 min/time, five times a week. Reward strategies refers to personalized active exercise programs for patients during hospitalization and at home. Patients can voluntarily choose tasks for active exercise and self-report to the therapist so as to punch a card for points and exchange gifts. The conventional group will receive home rehabilitation instructions prior to discharge. Rehabilitation motivation, measured using RMS. RMS, FMA, FIM, and ICF activity and social engagement scale will be compared at baseline, 3 weeks, 6 weeks, and 3 months post-enrollment to evaluate patients’ multifaceted health condition based on the ICF framework.

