Despite the existence of various interventions to stimulate patients’ motivation toward recovery, improvements are necessary. First, most approaches focus only on patients’ motivation during treatment, with little attention given to the maintenance of motivation post-treatment (42). Yet, the maintenance of high motivation is most critical for patients with chronic disease, as it directly influences their propensity to initiate unsupervised exercise. Second, the cost-effectiveness, healthcare resource consumption, treatment frequency, availability, acceptability, and generalizability of all current motivational interventions need to be examined and enhanced. Third, there is a lack of interventions targeting secondary alterations in stroke, such as functional decline in brain areas associated with motivation and the associated dysfunctional brain network connections. Future efforts should consider combining motivational interventions from multidisciplinary sources. Last but not least, a comprehensive approach to assessing motivation in stroke patients is lacking. A standardized process for evaluating rehabilitation motivation should be established.

Given this content, our team has designed a simple and resource-efficient treatment plan involving a reward strategy combined with a neuromodulation treatment. We aim to modulate patients’ brain neural activity via tDCS, enhancing the functional connectivity of brain regions linked to goal-directed behavior and the reward system. In addition, we plan to collaborate with patients to set treatment goals and offer external rewards to acknowledge their autonomy and self-drive in completing exercises. This approach aims to stimulate their intrinsic motivation and maintain the initiative of the rehabilitation program throughout the “hospital, home, and society” continuum.

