### 1.1. Objectives

This randomized controlled trial intends to evaluate the effectiveness of reward strategies combined with tDCS (RStDCS) in improving rehabilitation motivation in 87 patients with chronic stroke (onset over 6 months), compared to RS group without tDCS and conventional treatment group. Through this pilot study, we aim to verify whether reward strategies designed to boost rehabilitation motivation can provide a feasible approach throughout the entire “hospital, home and society” rehabilitation process. The primary objective is to compare the scores of rehabilitation motivation scale and the frequency of patients participating in unsupervised exercises at baseline, 3 weeks, 6 weeks after treatment, and at a 3-month follow-up. The secondary objective is to evaluate the structure and function, activities, and participation of patients within the framework of ICF to observe whether reward strategies can improve rehabilitation motivation, motor ability, daily living ability, and quality of life through self-reporting and assessment instruments.

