## 2. Methods and analysis

### 2.1. Study design

The reward strategy combined with tDCS treatment (RStDCS) for improvement of rehabilitation motivation after stroke study is a randomized, single blind, controlled clinical trial. Subjects will be randomly assigned to either the RStDCS group, the reward strategy with sham tDCS treatment group (RS group), or the conventional treatment with sham tDCS treatment (Control group). All patients will receive either true or sham tDCS stimulation and will be provided with an exercise program manual (content varies based on different requirements). Evaluators and statisticians will remain blind to the subjects’ group assignments. Assessments will be conducted at 0, 3, and 6 weeks and followed up at 3 months using assessment scales and behavioral observations. Prior to the assessment, the evaluator will be trained. Assessment scales include the Rehabilitation Motivation Scale (RMS), Fugl-Meyer Assessment Scale (FMA), Function Independent Measure (FIM), and ICF Activity and Participation Scale (ICF). Table 1 shows the schedule of enrollment, interventions, and assessments.

**Table 1 tab1:** The schedule of enrolment, interventions, and assessments.

	Study period				
	Enrolment	Allocation	Post-allocation		Close-out
Timepoint**	*−1 day*	0 day	*3 weeks*	*6 weeks*	*3 months*
Enrolment:					
Eligibility screen	X				
Informed consent	X				
Allocation		X			
Interventions:					
Group A (RStDCS)					
Group B (RS + sham)					
Group C (Conventional + sham)					
Assessments:					
RMS		X	X	X	X
FMAS		X	X	X	X
FIM		X	X	X	X
ICF		X	X	X	X

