**Figure 2 fig2:**
[figure not shown]
Groups overview and research implementation process.

In contrast, the RS group undergoes upper extremity rehabilitation with reward strategies and sham tDCS stimulation, identical in position to the RStDCS group. The current is ramped up and then immediately ramped down in the sham condition in 60 s to mimic the perception of current onset.

Reward strategies involve offering extrinsic rewards in recognition of patients’ independent performance encouraging sustained active rehabilitation motivation. Specifically, a 21-day inpatient-training manual is developed for chronic stroke patient with upper limbs dysfunction and low motivation. Upon discharge, a 21-day home training program is customized for each patient. Figure 3 shows the schematic diagram of reward strategy self-monitor brochure in in-patient and out-patient settings. Both program are tailored according to the Brunnstrom stage of upper limbs and hands, passive range of motion (PROM), muscle tone, muscle strength, fine motor abilities, grip strength, and activities of daily living (ADL). They incorporate exercises to improve and maintain joint mobility, therapeutic exercises, functional training, and ADL training. The Supplementary File 3 shows the contents of the library of active exercise program.

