### 2.6. Outcomes measures

Patients are evaluated at baseline, 3 and 6 weeks and at a 3-month follow-up using assessment scales and behavioral observations. Basic data (gender, age, disease duration, affected side, etc.) are extracted from electronic medical records. All data are entered into the paper Case Report Form (CRF) and uploaded to a protected research server online. The assessors are trained prior to data collection. Assessment scales include Rehabilitation Motivation Scale (RMS), Fugl-Meyer Assessment Scale (FMA), Function Independent Measure (FIM), ICF Activity, and Participation Scale (ICF).

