#### 2.6.2. Secondary outcome measures

The FMA, created by Swedish doctor Fugl-Meyer on the basis of Brunnstrom rating Scale in 1980. It is a widely recognized and frequently used, with proven reliability and validity (47). FMA can help to monitor and measure the level of ICF structure and function in patients. The FIM, proposed by researchers from the Functional Assessment Research Center of New York State in 1987, assesses the ADL ability of stroke patients comprehensively and objectively (48). The ICF Activity and Participation Scale appraises the health status and health-related condition over the past 30 days covering six areas: understanding and communication, physical activity, self-care, interpersonal interactions, life activity, and social participation. Both FIM and ICF Activity and Participation can measure the level of ICF Activity and Participation level.

Behavioral observation data included the number of therapist-supervised active exercise sessions during hospitalization and the number of self-reported active exercise sessions by patients at home. After 42 days of reward training, the researchers collect the program manual and tally the number of completed sessions.

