#### 2.8.2. Statistical analyses

SPSS 26.0 version will be used for data analysis. Chi-square tests are used to compare count data, and descriptive statistical analyses is conducted to study the basic information of subjects in RStDCS group, RS group, and control group. Independent sample *t* tests will be used for intergroup comparisons of measurement data following a normal distribution, while paired sample *t* tests will be used for intragroup comparisons, represented as “(
$\bar{x}$
±s).” If the data do not follow a normal distribution, independent sample rank sum tests will be used for intergroup comparisons, and paired sample rank sum tests for intragroup comparisons, represented as [M (P25, P75)]. To investigate the impact of using reward strategies combined with neuromodulation techniques on upper limb dysfunction in chronic stroke survivors with low motivation over time, a repeated measure ANOVA will be performed, with rehabilitation motivation, motor function, functional independence, ICF activity, and participation as dependent variables. The model includes three groups (RStDCS group, RS group, and control group) and three test types (0, 3, and 6 weeks). Due to the strict requirements for repeated measurement data, missing cannot occur. If a sample lacks measurement data, all the data from that sample will be excluded from the model during analysis. A value of *p* less than 0.05, two-tailed, is considered statistically significant.

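### The repeated-measures model stops at 6 weeks, and no test is assigned to the 3-month visit, which is in the primary objective and is the only visit after rewards end

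*Protocol article*

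**What the plan says.** **Objective and schedule.** In the protocol article, section 1.1 sets the primary objective as a comparison of RMS scores and exercise frequency "at baseline, 3 weeks, 6 weeks after treatment, and at a 3-month follow-up". The abstract says that the four scales "will be compared at baseline, 3 weeks, 6 weeks, and 3 months post-enrollment". Section 2.1 states "Assessments will be conducted at 0, 3, and 6 weeks and followed up at 3 months", and Table 1 marks RMS, FMA, FIM and ICF at all four times. Section 2.6 agrees: "Patients are evaluated at baseline, 3 and 6 weeks and at a 3-month follow-up using assessment scales".

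**Intervention period.** Stimulation covers the 3 inpatient weeks. The reward programme has a 21-day inpatient part, and then, under section 2.5, "Upon discharge, a 21-day home training program is customized for each patient". Section 2.6.2 gives the end point: "After 42 days of reward training, the researchers collect the program manual and tally the number of completed sessions". Points are redeemed when the programme closes.

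**Analysis.** Section 2.8.2 describes one longitudinal model, a repeated-measures ANOVA with three groups "and three test types (0, 3, and 6 weeks"). It also lists t tests or rank-sum tests between and within groups, without naming a visit. A patient with any missing measurement is removed from the model entirely.

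**Sample size.** Section 2.8.1 uses the within-between interaction of a repeated-measures ANOVA and arrives at 72 completers, or 87 after 15% dropout. It does not state the number of measurements.

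**The concern.** The analysis section states its time points and leaves out one that the primary objective names. This is a contradiction between two stated parts of the document, not a detail left to a fuller plan.

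The missing visit also bears most directly on the trial's rationale. The introduction criticises existing approaches for focusing on the treatment period, "with little attention given to the maintenance of motivation post-treatment". On the clock used in the abstract and section 2.1, week 6 falls on the last day of the reward programme. A model that ends there can show whether motivation is higher while rewards are on offer. It cannot show whether the difference lasts once they stop.

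If the plan is run as written, a statement about lasting motivation would rest on a visit-level test chosen after the fact. There are three possible arm comparisons and no rule on which of them counts.

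**Working it through.** **1. Time line, counted from enrolment**

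| Visit | Stimulation | Rewards | In the model of 2.8.2? |
|---|---|---|---|
| Baseline | not started | not started | yes |
| 3 weeks (day 21) | ends | inpatient part ends | yes |
| 6 weeks (day 42 = 21 + 21) | ended 3 weeks before | home part ends | yes |
| 3 months | ended | ended | **no** |

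**2. Reproducing the stated N**

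Inputs from 2.8.1: f = 0.25, k = 3 groups, correlation 0.5, epsilon 0.5, alpha 0.05, power 0.90. The number of measurements m is not stated, so it is varied. The G*Power formulas for the within-between interaction are:

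- λ = f² · N · m · ε / (1 − ρ)
- df1 = (k − 1)(m − 1)ε
- df2 = (N − k)(m − 1)ε

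For m = 3 and N = 72: λ = 0.0625 × 72 × 3 × 0.5 / 0.5 = 13.5, df1 = 2 × 2 × 0.5 = 2, df2 = 69 × 2 × 0.5 = 69. Power is 0.906. The value 0.90 is first reached at N = 71, which equal groups round up to 72. Then 24 / 0.85 = 28.2, rounded up to 29 per group, or 87. Both stated figures reproduce.

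Other values of m do not give 72. With m = 4 the required N is 60. With m = 2, where epsilon must be 1, it is 54. The sample size was therefore built on three measurements, which argues against a typing slip in 2.8.2.

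**3. The same calculation with four visits**

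Epsilon cannot fall below 1/(m − 1). At m = 3 that bound is 0.5, so the plan used the most conservative value for three visits. At m = 4 the bound is 1/3.

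| ε (m = 4) | λ at N = 72 | df1, df2 | Power at 72 | N for 0.90, equal groups |
|---|---|---|---|---|
| 0.5 (plan's figure) | 18.0 | 3, 103.5 | 0.952 | 60 |
| 1/3 (lower bound, assumed) | 12.0 | 2, 69 | 0.868 | 81 |

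At the lower bound, 81 completers are 27 per arm. 27 / 0.85 = 31.8, rounded up to 32 per arm, or 96 enrolled against 87 planned.

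**4. Power for the 3-month question itself**

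The figures in step 3 are for the omnibus interaction, which can be significant because of weeks 3 and 6 alone. The sustained effect is a between-arm contrast at one visit. For a two-sample t test with 24 per arm (72 / 3), two-sided 0.05, no multiplicity adjustment, the noncentrality is d · √(24/2):

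- d = 0.5 (assumed): 1.73, power about 0.40
- d = 0.8 (assumed): 2.77, power about 0.77

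**The case against.** **The t or rank-sum tests cover 3 months.** They can. Section 2.8.2 does not restrict them to a visit, and a two-arm comparison at one visit is valid under randomisation. A reader might infer that the 3-month data are never tested at all; the document does not support that. What stands is narrower. No test, contrast or multiplicity rule is assigned to that visit, and the model used for the sample size omits it. The document does not label the repeated-measures ANOVA the main analysis. Its weight comes from being the only longitudinal model and the basis of N.

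**The model is not blind to persistence.** This is partly right. Stimulation ends at week 3, so the combined arm against the reward-only arm at week 6 already looks three weeks past stimulation, and week 6 follows an unsupervised home phase. The gap concerns what happens after rewards end.

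**Section 1.1 speaks of 6 weeks after treatment.** Read literally, that could move the visit past the rewards. The abstract, section 2.1 and the 42-day programme point to the enrolment clock. On either reading the 3-month visit is in the objective and outside the model.

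**It is a pilot study.** Section 1.1 does use the term. That lowers the weight of any single test, but it does not reconcile the objective with the analysis.

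**Adding the visit is free.** A reader might infer this from the power of 0.95 at 72 completers. The documents do not support it. That figure carries epsilon 0.5 over from three visits, where it was the worst case, and it concerns the omnibus test, not the 3-month contrast.

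**Conclusion.** The concern holds in this form: the longitudinal model in 2.8.2 ends on the last day of the reward programme, and no test is assigned to the one visit after it, although the primary objective names that visit. The sample size carries the same omission, since 72 reproduces only with three measurements.

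With four visits, the 72 planned completers give omnibus power between 0.87 and 0.95, and the required N runs from 60 to 81, depending on epsilon between 1/3 and 0.5. A single unadjusted 3-month contrast has much less power, about 0.40 at d = 0.5. These results rest on the plan's effect size and correlation, on visits counted from enrolment, and on the assumed values of epsilon at its four-visit bound and of d.

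**What to change.** **Section 2.8.2.** Define the model as three groups by four visits (0, 3 and 6 weeks, 3 months). Prespecify the between-arm RMS contrasts at 3 months as the test of the sustained effect, and state a multiplicity rule for the arm comparisons.

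**Missing data, in the same section.** Replace listwise deletion with a likelihood-based mixed model for repeated measures. If the present rule stayed, a fourth visit would remove every patient missing at 3 months from the comparisons at 3 and 6 weeks as well.

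**Section 2.8.1.** State the number of measurements. Give power for 72 completers as a range (0.95 at epsilon 0.5, 0.87 at 1/3) and say that it refers to the omnibus interaction. Report the power of a 3-month pairwise contrast separately, with its assumed effect size.

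**Cost.** The 3-month assessments are already in Table 1, so the change is to the text of these two sections. The price is some extra missing data at the later visit and a less favourable stated power. The sponsor would also have to decide whether 87 enrolled patients is enough for the sustained-effect question or whether that contrast should be reported as exploratory.

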### 2.8. Statistics

#### 2.8.1. Sample size

Sample size estimation was made assuming a medium effect size (0.25) seen in previous similar studies (49, 50). G*power software (3.1.9) is used with the means of ANOVA Repeated measures, within-between interaction. The type of power analysis is *a priori*: compute required sample size-given α, power, and effect size. The calculation indicated a sample size of 72 subjects with a desired power of 0.90 at a 5% significance (two-tailed), correlation coefficient of 0.5, and nonsphericity correction of 0.5. Factoring in a 15% dropout rate, we estimated that each group should comprise 29 subjects, making a total of 87 subjects across the three groups.

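### The repeated-measures ANOVA drops every patient with a gap at weeks 0, 3 or 6, making the main longitudinal comparison completers-only although 15% dropout is expected

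*Protocol article*

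**What the plan says.** Section 2.8.2 of the protocol article names one longitudinal model: "a repeated measure ANOVA will be performed, with rehabilitation motivation, motor function, functional independence, ICF activity, and participation as dependent variables". Its factors are the three groups and "three test types (0, 3, and 6 weeks"). The section then gives a premise, "Due to the strict requirements for repeated measurement data, missing cannot occur", and a rule that follows from it: "If a sample lacks measurement data, all the data from that sample will be excluded from the model during analysis".

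Section 2.8.1 bases the sample size on the same kind of test, "ANOVA Repeated measures, within-between interaction". It raises the 72 patients required to 87: "Factoring in a 15% dropout rate".

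Three other places bear on this:

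- Section 2.3 admits only patients with a Rehabilitation Motivation Scale (RMS) score of 25 or less, and section 2.6.1 makes the RMS the primary outcome.
- The Introduction links apathy to reduced or refused participation in exercise.
- Section 2.5 lets patients in the two reward arms exchange points for gifts (up to 267 RMB) when the programme ends. The control arm has no rewards.

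**The concern.** The rule is written into the plan, so it is not a detail left open for a statistical analysis plan. It has two faults.

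First, its premise is mistaken and sits badly with the rest of the plan. Only the classical repeated-measures ANOVA needs complete records; repeated-measures data as such do not. Declaring that gaps cannot happen also contradicts an allowance of 15% for dropout.

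Second, it changes who is compared. Randomisation makes the three groups comparable as allocated; deletion compares those who attended every modelled visit. In patients chosen for low motivation, with motivation as the outcome, attendance is plausibly linked to outcome. The reward programme lasts 21 + 21 = 42 days, so the gifts fall due at about week 6, the last visit in the model. That gives the reward arms a reason to stay that control patients lack. If selection differs between arms, the difference enters the estimated group effect. Inflating the sample size replaces numbers but does not undo selection.

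**Working it through.** **1. The plan's own figure.** Inputs from section 2.8.1: f = 0.25, α = 0.05, power 0.90, correlation ρ = 0.5, nonsphericity correction ε = 0.5, k = 3 groups. From section 2.8.2: m = 3 visits. For the within-between interaction:

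- λ = f²·N·m·ε/(1−ρ) = 0.0625 × 72 × 3 × 0.5/0.5 = 13.5
- df1 = (k−1)(m−1)ε = 2 × 2 × 0.5 = 2
- df2 = (N−k)(m−1)ε = 69 × 2 × 0.5 = 69

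The noncentral F gives power 0.906 at N = 72. The smallest N reaching 0.90 is 71, or 72 as a multiple of three, so the stated 72 is reproduced. Dropout: 24/(1−0.15) = 28.2, rounded up to 29 per group and 87 in total, also reproduced.

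**2. What the expected dropout does.** 87 × 0.15 = 13.05 patients leave the model and 87 × 0.85 = 73.95, about 74, remain. Power at 74 is 0.914, so the planned power survives. At 20% loss (70 patients) it would be 0.897, and at 25% (65 patients) 0.872.

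**3. Scattered missed visits.** The model has two post-baseline visits. If a share p is missing independently at each (an assumption), the rule deletes 1 − (1−p)²:

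- p = 5%: 1 − 0.95² = 9.8%
- p = 10%: 1 − 0.90² = 19%, leaving about 70.5 of 87

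**4. Possible bias.** The documents give neither dropout by arm nor its cause, so these inputs are assumed: no true effect, scores at weeks 0, 3 and 6 with SD 1 and correlation 0.5, and dropout after week 3 with log-odds rising by 1.5 per SD of a poorer week-3 value. One arm loses 15% and another 25%. The scale that matters is change from baseline, because week 0 is a level of the time factor and the trial is powered on the interaction. Completers' mean change, in SD (simulated):

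| Dropout driven by | Visit | Arm losing 15% | Arm losing 25% | Bias in group difference |
|---|---|---|---|---|
| Week-3 level | Week 3 | 0.09 | 0.14 | about 0.05 |
| Week-3 level | Week 6 | 0 | 0 | 0 |
| Poor week-3 change | Week 3 | 0.18 | 0.28 | about 0.10 |
| Poor week-3 change | Week 6 | 0.09 | 0.14 | about 0.05 |

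The bias favours the arm that loses more patients. With 15% dropout by the same mechanism in both arms, the bias is about zero. With dropout driven by poor change, slopes of 1 to 2, and imbalances from 20% versus 10% up to 30% versus 5%, the bias runs from 0.08 to 0.30 SD at week 3 and from 0.04 to 0.15 SD at week 6. Using the dropouts' observed baseline and week-3 scores brings the week-6 bias to about zero in all these scenarios.

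**The case against.** The strongest reply is that the loss has been budgeted, that the article calls the trial a pilot, and that the bias may be small or absent. Much of this stands, and it rules out several stronger readings that a reader might infer.

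- *The trial is underpowered by the deletions.* Not at the stated 15%, as step 2 shows. The 13 patients are the planned allowance and no further loss.
- *Patients vanish from every analysis.* The rule speaks of the model, that is, the repeated-measures ANOVA. No deletion rule is stated for the t tests and rank-sum tests in the same section.
- *A missed 3-month visit also deletes the patient.* That visit is not in the model. Counting three post-baseline visits would give 14% or 27% deleted (1 − 0.95³, 1 − 0.90³), but those figures do not describe this plan.
- *An arm's completers' shift goes straight into the group difference.* With dropout driven by the week-3 level, completers in an arm losing 25% stand 0.28 SD too high at week 3 and 0.14 SD at week 6. Those are levels within one arm. Baseline shifts too, by 0.14 SD, and only the difference between arms reaches the comparison.
- *Deletion is biased unless data are missing completely at random.* Too strong: equal dropout by one mechanism gives about no between-arm bias, and dropout on the week-3 level gives none in week-6 change.
- *The gifts distort every contrast.* Both reward arms have the same rewards, so the argument applies against control and gives no reason for unequal dropout in the contrast that isolates tDCS.

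None of this rescues the rule. It is harmless only under conditions that the plan cannot assure, and the one-sided reward works against equal retention in the comparisons with control. The pilot label does not help either, since the trial tests efficacy at the 5% level.

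**Conclusion.** The concern holds in a bounded form. The rule rests on a wrong premise, conflicts with the plan's own dropout allowance, and turns the main longitudinal comparison into one of completers at weeks 0, 3 and 6. The harm is possible bias and loss of the randomised comparison, with planned power intact at 15% loss.

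In the 25% versus 15% example the bias in the group difference in change lies between 0 and about 0.10 SD, depending on visit and mechanism. It is larger if the imbalance is larger and near zero if dropout rate and mechanism match across arms. These sizes rest on an assumed visit correlation, dropout slope and dropout rates by arm. The documents support the plausibility of selective dropout, but not its size or direction.

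**What to change.** Replace the deletion rule and the repeated-measures ANOVA in section 2.8.2 with a likelihood-based linear mixed model that analyses patients as randomised and uses all observed visits, with group-by-visit terms.

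Preferably keep baseline as a response with a common mean across arms, so that patients with only a baseline visit stay in. Baseline as a covariate is acceptable, but patients with no post-baseline visit then contribute nothing.

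Delete the sentence saying that missing data cannot occur, report missingness by arm and visit, and keep the complete-case ANOVA as a supportive analysis. The model is valid if missingness depends only on observed scores; a sensitivity analysis for data missing not at random is an optional addition.

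The cost is a change of wording, made before unblinding, and a little more analysis work. The mixed-model procedure in SPSS, the package already named, can fit the covariate form. No new data are needed and the sample size stays as it is.
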